Internet of Things (IoT) technology, enabling real-time data exchange between patients and healthcare providers through interconnected devices and platforms, represents a significant advancement in contemporary healthcare delivery (16). Although IoT has been explored for continuous vital sign monitoring in COPD management (17–20), existing evidence for PR is limited, especially for patients with moderate-to-severe COPD and a history of exacerbations. Most studies are characterized by small sample sizes and short follow-up periods, precluding robust assessment of long-term clinical outcomes. Moreover, substantial heterogeneity in intervention design has hindered the development of a standardized IoT-based PR management model (21).

In response to these gaps, the present study aims to conduct a prospective cohort investigation to develop and evaluate an IoT-based PR management model and to assess its impact on clinical outcomes in patients with moderate-to-severe COPD. The specific objectives are as follows: (1) to compare the effect of an IoT-assisted PR management model versus conventional care on the rate of AECOPD-related readmissions within 12 months post-discharge; (2) to evaluate the model’s efficacy in improving exercise tolerance, dyspnea, HRQoL, pulmonary function, and rehabilitation adherence; and (3) to examine the safety and feasibility of IoT-assisted PR management, thereby providing evidence-based support for clinical practice.

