### Study design

2.1

This is a prospective, pragmatic, non-randomized controlled intervention study with a 52-week follow-up period. The intervention is actively assigned based on patient preference and technology readiness, and the study includes a concurrent control group receiving standard care. The study protocol has been registered with the Chinese Clinical Trial Registry (ChiCTR2500106412). Study design and reporting will adhere to the Standard Protocol Items: Recommendations for Interventional Trials (SPIRIT) guidelines (22). Figure 1 is the trial flow chart.

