#### Inclusion criteria

2.2.1

Age between 40 and 75 years.A confirmed diagnosis of COPD according to GOLD criteria, defined as a post-bronchodilator FEV₁/FVC ratio < 0.70 and FEV₁ % predicted < 80% (GOLD grades 2–4) at enrollment.A history of at least two moderate acute exacerbations or one severe acute exacerbation requiring hospitalization within the preceding 12 months (Group E according to the GOLD guideline).Clinical stability for a minimum of four weeks prior to enrollment, defined as the absence of acute exacerbations or changes in pharmacological regimen.Capacity to provide written informed consent and willingness to comply with all study procedures, including utilization of IoT devices and the smartphone application.

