### Statistical analysis

3.4

Data will be analyzed using SPSS version 23.0 and R (version 4.2 or above). The following analytical approaches will be employed:

(1) Data description: continuous variables will be assessed for normality using appropriate statistical tests. Normally distributed data will be expressed as mean ± standard deviation (x̄ ± s); non-normally distributed data will be presented as median (interquartile range). Categorical variables will be summarized as frequencies (*n*) and proportions (%).(2) Between-group comparisons: categorical variables will be compared using the chi-square test or Fisher’s exact test, as appropriate. Normally distributed continuous variables will be analyzed using the independent samples t-test; within-group pre-post comparisons will employ the paired t-test. Non-normally distributed variables will be analyzed using non-parametric equivalents (Mann–Whitney U test or Wilcoxon signed-rank test). Multiple group comparisons will utilize one-way analysis of variance (ANOVA) with appropriate post-hoc correction (LSD or Bonferroni). Longitudinal data across repeated time points will be analyzed using repeated measures ANOVA or generalized estimating equations (GEE).(3) Multivariable analysis: to delineate the independent association between the IoT intervention and primary outcome measures (e.g., pulmonary function improvement, AECOPD frequency, readmission rate), multivariable logistic regression or Cox proportional hazards models will be employed, with adjustment for pre-specified potential confounders (including age, sex, comorbidities, and smoking history).(4) Missing data: missing data for key variables will be addressed using single and multiple imputation techniques to preserve sample integrity and maximize analytical efficiency.(5) Significance threshold: all statistical tests will be two-sided, with a significance level of *p* < 0.05. Where applicable, multiple testing corrections (e.g., Bonferroni correction) will be implemented to control the family-wise type I error rate.

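### Within-group before-after tests are planned as inferential tests and not marked as descriptive, while objective 2 names no comparator, so change unrelated to the IoT model could be reported as efficacy

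*Protocol article*

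**What the plan says.** Section 3.4, item (2), is headed as between-group comparisons. It first gives the comparison between arms: "Normally distributed continuous variables will be analyzed using the independent samples t-test". The same sentence continues: "within-group pre-post comparisons will employ the paired t-test". For non-normal data it names the Mann–Whitney and Wilcoxon signed-rank tests, and for repeated time points repeated-measures ANOVA or GEE. Item (5) applies a two-sided 0.05 threshold to all tests. No sentence limits the paired tests to description.

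The Introduction words the first two objectives differently. Objective 1 is comparative: "to compare the effect of an IoT-assisted PR management model versus conventional care". Objective 2 is "to evaluate the model’s efficacy in improving exercise tolerance, dyspnea, HRQoL, pulmonary function, and rehabilitation adherence", with no comparator.

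Section 2.2.1 requires "A history of at least two moderate acute exacerbations or one severe acute exacerbation requiring hospitalization within the preceding 12 months", and also "Clinical stability for a minimum of four weeks prior to enrollment". Section 2.1 states that "the study includes a concurrent control group receiving standard care". Both arms receive education and a home exercise prescription (sections 2.5.1 and 2.5.2), allocation follows preference and technology readiness (section 2.4), and participants are not blinded (limitations in the Discussion).

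**The concern.** A paired test asks whether the mean change in one arm differs from zero. It cannot say why. Here several causes other than the IoT model can move 6MWD, mMRC, CAT, SGRQ or spirometry: natural course after a year with exacerbations, the education and exercise prescription given to both arms, and expectation in unblinded patients. A p-value from this test therefore carries no information about the IoT model as such.

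The wording of objective 2 makes this matter. A significant change in Group B alone would fit its wording even if Group A had changed just as much. A second temptation is to contrast a significant change in Group B with a non-significant one in Group A, which is not a test of the difference between the arms. The claims at stake are those on secondary outcomes. The primary outcome is not affected, because it is a count of events during follow-up (section 3.1.1.1).

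**Working it through.** **Inputs.** From section 2.3: 267 patients per group before attrition, two-sided alpha 0.05, planned reduction 20%, and 0.5 to 3.0 exacerbations a year of which about 60% are moderate or severe. Assumed, because the article gives no figure: the size of the drift and the spread of exacerbation rates between patients.

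**The plan's own 267.** Two proportions of 0.60 and 0.48 (RR 0.80) with unpooled variance give 7.849 × (0.24 + 0.2496) / 0.12² = 266.9, so 267, and 267 × 1.10 = 293.7, so 294. This requires reading the 60% as a control event proportion. That does not bear on the present point, where 267 serves only as the group size.

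**Paired test with zero IoT effect.** Let both arms drift by the same d, in units of the SD of the change. The paired t statistic follows a noncentral t distribution with 266 degrees of freedom and noncentrality d × √267 = 16.34d. Let p be its two-sided rejection probability. With independent arms, the chance of significance in B but not in A is p(1 − p). A common drift cancels in the between-group difference, so that test rejects at its nominal rate.

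| Assumed drift d | Noncentrality | p: Group B paired test significant | Significant in B, not in A | Between-group test significant |
|---|---|---|---|---|
| 0 | 0 | 0.05 | 0.048 | 0.05 |
| 0.1 | 1.63 | 0.370 | 0.233 | 0.05 |
| 0.2 | 3.27 | 0.903 | 0.088 | 0.05 |
| 0.3 | 4.90 | 0.998 | 0.002 | 0.05 |

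The drift that a paired test detects with 80% power is about 2.80 / √267 = 0.171 SD.

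**Regression to the mean, as an illustration of the mechanism only.** Suppose yearly counts are Poisson with gamma-distributed patient rates of mean μ and shape k, and patients enter with two or more events. The mean count before is E[Y | Y ≥ 2]. The mean in the next year, untreated, is (k + that value) / (k/μ + 1). The means used are 1.75 × 0.60 = 1.05 (mid-range) and 3.0 × 0.60 = 1.8 (top of the range).

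- μ = 1.05, k = 1: the probabilities of 0 and 1 event are 0.488 and 0.250, so before = (1.05 − 0.250) / 0.262 = 3.05 and after = 4.05 / 1.952 = 2.07, a drop of 32%.
- μ = 1.05, k = 2: 2.75 to 1.64, a drop of 41%.
- μ = 1.8, k = 1: 3.80 to 3.09, a drop of 19%.
- μ = 1.8, k = 2: 3.34 to 2.53, a drop of 24%.

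Selection on event history can thus produce a sizeable fall without treatment. These figures concern exacerbation counts. They do not measure drift in the continuous outcomes that the paired test would reach.

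**The case against.** The strongest reply is that the study is comparative. It has a concurrent control under the same entry criteria, objective 1 names that control, item (3) of section 3.4 assigns the intervention effect to adjusted models, and the Discussion adds propensity score and sensitivity analyses. The paired test is one clause among these. Objective 2 stands in the same list as objective 1, so its missing comparator may be loose drafting. This stands in part. A reader might infer that the plan will read recovery or regression to the mean as efficacy, but no sentence says so.

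A reader might also set the 19% to 41% drops in exacerbations against the planned 20% effect. That does not hold. The plan does not say that prior-year and follow-up counts will be paired, and a before-after drop is not comparable with a between-group ratio, from which a common drift cancels. For the secondary outcomes regression to the mean is indirect, and the documents give no size for it.

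Nor do the documents show that patients enter at a peak. The qualifying event may be up to 12 months old, and four weeks of stability limit early recovery. The article also dates the home prescription from discharge (sections 2.5.1.2 and 2.5.2). That sits uneasily with the stability rule, and the passages must be reconciled.

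Finally, an analysis plan that is not shown might label the paired tests as descriptive. But the article states them as tests under a 0.05 threshold, so this is a stated choice rather than a detail left out. None of the replies makes a within-group p-value informative about the IoT model.

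**Conclusion.** The point holds as a weakness in what the plan permits. Section 3.4 provides within-group significance tests, objective 2 names no comparator, and nothing prevents the one from being used to answer the other. With no IoT effect, an assumed common drift of 0.2 SD makes the Group B paired test significant about 90% of the time, and 0.1 SD already does so 37% of the time. At 0.1 SD, significance in B but not in A arises by chance in 23% of studies.

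These rates rest on 267 patients per group, independent arms, approximately normal changes and drift sizes that are assumptions. The 5% rate for the between-group test also assumes equal drift in both arms. Allocation by preference may break that assumption, so the between-group comparison needs adjustment. Prior exacerbation history is collected (section 3.2) but is not among the confounders named as examples in section 3.4, item (3). The consequence is confined to claims on secondary outcomes.

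**What to change.** In section 3.4, item (2), remove the paired t-test and the Wilcoxon signed-rank test as inferential tests. Report within-group changes descriptively and state that they are not evidence of efficacy. That statement is needed even if intervals are shown, because a 95% interval for the mean change that excludes zero is the same result as a paired t-test at 0.05.

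State that efficacy under objective 2 rests on the between-group difference at each scheduled visit where the outcome is measured. This keeps the one-month visit for spirometry and questionnaires, while 6MWD is measured at 3, 6 and 12 months. The estimate should come from the planned longitudinal model, adjusted for the baseline value of that outcome, prior exacerbation history and the confounders promised in sections 2.4 and 3.2 and in the Discussion, including digital literacy, baseline motivation and socioeconomic status. Exempt adherence: section 3.1.2 defines it for the intervention group only, so it is reported descriptively.

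The change uses data already to be collected and needs no new visit or patient. Its cost is that within-group p-values can no longer be cited as efficacy.

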## Abstract

Pulmonary rehabilitation (PR) constitutes a cornerstone of non-pharmacological management in chronic obstructive pulmonary disease (COPD); however, its clinical effectiveness is frequently attenuated by suboptimal patient adherence and the absence of individualized, continuous monitoring within the home setting. Internet of Things (IoT) technology offers a promising solution to these persistent challenges; however, comprehensive closed-loop management models that fully integrate IoT capabilities remain underexplored. This prospective, non-randomized controlled intervention study will enroll 588 patients with moderate-to-severe stable COPD (GOLD grades 2–4) from a single institution. Participants will be assigned to either conventional PR (Group A) or IoT-assisted PR (Group B) based on initial preference and technology readiness. Group B will receive IoT-enabled devices and a smartphone app to support home-based PR, including daily respiratory muscle training and structured aerobic/resistance exercise (3–5 sessions/week). Group A will receive standard PR education and guidance. Follow-ups will occur at weeks 4, 12, 26, and 52. The primary outcome is the 12-month rate of moderate-to-severe AECOPD. Secondary outcomes include pulmonary function, exercise capacity, HRQoL, right cardiac function, pneumonia incidence, all-cause mortality, and adherence. Analyses will be performed on an intention-to-treat basis. This study will evaluate the efficacy of an IoT-based pulmonary rehabilitation management model in reducing AECOPD-related readmissions and improving exercise tolerance, quality of life, and dyspnea in patients with moderate-to-severe COPD, while examining its feasibility and safety in a real-world setting. The findings may support the development of a technology-enabled continuous care model for chronic respiratory diseases, facilitating the transition from hospital-centric to patient-centric care and advancing the application of smart nursing and remote health management. The study protocol has been registered with the Chinese Clinical Trial Registry (ChiCTR2500106412).

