### Participant recruitment and group allocation

2.4

Eligible patients will be identified and recruited by clinicians within the Department of Respiratory and Critical Care Medicine at Shijiazhuang People’s Hospital. Research nurses will provide prospective participants with comprehensive information regarding the study. Given the inherent nature of the intervention—which necessitates active patient engagement with technology—strict randomization may compromise adherence and ecological validity. Therefore, following the provision of written informed consent, participants will be allocated to either the IoT-assisted PR group or the conventional PR group based on their initial preference and a preliminary assessment of technology readiness and digital competency (e.g., smartphone ownership, basic digital literacy). This pragmatic allocation approach is designed to reflect real-world implementation conditions. Participants who initially prefer conventional care but express willingness to engage with IoT technology will be encouraged to join the IoT-assisted PR group to maximize recruitment efficiency. Baseline characteristics of both groups will be rigorously compared and statistically adjusted in all subsequent analyses. We acknowledge that an attention-matched control group is not feasible in this pragmatic study design due to resource constraints and the inherent nature of the IoT intervention. This limitation will be discussed more clearly in the Discussion section.

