##### Follow-up assessments

2.5.1.3

Outpatient clinic visits will be scheduled at 1, 3, 6 and 12 months for clinical evaluation, spirometry, and questionnaire administration. No remote monitoring or proactive feedback regarding PR adherence will be provided during the follow-up period.

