#### Secondary outcomes

3.1.2

Exercise tolerance: assessed using the six-minute walk distance (6MWD), conducted in accordance with American Thoracic Society (ATS) guidelines along a 30-meter flat corridor. Measurements will be obtained at baseline and at 3, 6, and 12 months post-intervention.Dyspnea severity: evaluated using the modified British Medical Research Council (mMRC) dyspnea scale, a single-item, five-level ordinal scale (scored 0–4), with higher scores indicating greater dyspnea severity.Health-related quality of life: assessed jointly using the COPD Assessment Test (CAT) and the St. George’s Respiratory Questionnaire (SGRQ). The CAT comprises 8 items with a total score ranging from 0 to 40, where higher scores indicate worse HRQoL. The SGRQ comprises 50 items encompassing symptoms, activity limitation, and disease impact domains, with a total score ranging from 0 to 100, where higher scores indicate worse HRQoL.Pulmonary function: measured using a portable spirometer, capturing FEV₁ % predicted, FVC, and peak expiratory flow (PEF). All measurements will be performed by trained research nurses according to standardized operating procedures.Rehabilitation adherence: in the intervention group, adherence will be assessed using the following metrics: (i) *device utilization adherence rate*, defined as daily data upload completion rate ≥ 80%; (ii) *training completion rate*, calculated as the number of days on which prescribed rehabilitation was completed divided by the total prescribed training days, multiplied by 100%; and (iii) *follow-up completion rate*, defined as the proportion of participants completing assessments at each scheduled timepoint.Adverse events: all adverse events occurring during the study period will be systematically recorded, including but not limited to falls, fractures, or cardiovascular events associated with rehabilitation training; disease deterioration events; and unplanned healthcare utilization events.

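### The between-group methods named for 6MWD, CAT, SGRQ and spirometry allow an analysis that mishandles the baseline value, and the adjusted models named do not fit these outcomes

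*Protocol article*

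**What the plan says.** Protocol article, section 3.4, item (2), sets the between-group methods for continuous outcomes. For single comparisons: "Normally distributed continuous variables will be analyzed using the independent samples t-test". For repeated visits: "Longitudinal data across repeated time points will be analyzed using repeated measures ANOVA or generalized estimating equations (GEE"). It does not choose between the two, state the role of the baseline value, or say whether the group term or group-by-time is the treatment test.

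Item (3) names multivariable logistic regression or Cox models for adjustment. Item (4) says that "missing data for key variables will be addressed using single and multiple imputation techniques to preserve sample integrity and maximize analytical efficiency", without listing the key variables. Section 2.4 promises: "Baseline characteristics of both groups will be rigorously compared and statistically adjusted in all subsequent analyses". The Discussion adds multivariable regression and propensity scores in general terms, without tying them to a continuous outcome.

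On timing, section 3.1.2 says of 6MWD: "Measurements will be obtained at baseline and at 3, 6, and 12 months post-intervention", which is three follow-ups. It gives no time points for CAT or SGRQ. Section 2.5.1.3 says for the control group: "Outpatient clinic visits will be scheduled at 1, 3, 6 and 12 months for clinical evaluation, spirometry, and questionnaire administration", so four follow-ups are assumed for the questionnaires.

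**The concern.** Objective 2 in the Introduction concerns improvement in exercise tolerance, dyspnoea, quality of life and lung function. For such outcomes the baseline value is the strongest single predictor of later values. Groups are formed by preference and technology readiness, and section 3.2 itself expects them to differ, so baseline values may be unequal.

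Two of the methods that item (2) permits can go wrong here. An unadjusted t-test ignores baseline. Repeated-measures ANOVA, if baseline is one of the responses and the group main effect is the test, averages in a visit at which no treatment effect can exist and carries any baseline imbalance into the estimate. Logistic and Cox models cannot supply the promised adjustment for repeated continuous scores. GEE could carry covariates, but the plan neither requires GEE nor says that it will.

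At stake are the estimates and tests of the secondary outcomes that carry objective 2. The primary exacerbation analysis is not affected.

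**Working it through.** **Inputs from the protocol article.** Two-sided alpha 0.05 (section 3.4); 267 per group before attrition and 10% attrition (section 2.3); m = 3 follow-ups for 6MWD (section 3.1.2); m = 4 assumed for CAT and SGRQ (section 2.5.1.3).

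**Assumptions.** The article gives no effect size, SD, correlation or power for any secondary outcome. I take unit SD at each visit, a common correlation rho of 0.5 to 0.8 between visits, and a constant effect d of 0.20 or 0.25 SD at all follow-ups.

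**The plan's own figure.** Section 2.3 sizes only the primary outcome. Its 267 is reproduced by a two-proportion formula with 0.60 against 0.8 × 0.60 = 0.48: 7.849 × (0.24 + 0.2496)/0.0144 = 266.9. I use 267 here only as a number of participants.

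**Group main effect with baseline as a level of time.**
- Expected value: b + [m/(m+1)]d. With b = 0 the factor is 3/4 = 0.75 for m = 3 and 4/5 = 0.80 for m = 4. This part needs no assumed SD or correlation.
- Variance of a participant's mean: V = (1 + m·rho)/(m + 1). Standard error: √(2V/n).
- m = 3, d = 0.25, rho = 0.5: V = 0.625, SE = 0.0684, 0.1875/0.0684 = 2.74, power 78%.
- Same with rho = 0.8: V = 0.85, SE = 0.0798, 0.1875/0.0798 = 2.35, power 65%.

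**Mean of follow-ups with baseline as covariate.**
- V = [1 + (m − 1)rho]/m − rho².
- rho = 0.5: V = 0.4167, SE = 0.0559, 0.25/0.0559 = 4.47, power 99.4%.
- rho = 0.8: V = 0.2267, SE = 0.0412, 0.25/0.0412 = 6.07, power above 99.9%.

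**Group-by-time test.** Noncentrality (n/2)d²[m/(m+1)]/(1 − rho).
- rho = 0.5: 133.5 × 0.0625 × 0.75/0.5 = 12.5, power about 85%.
- rho = 0.8: 31.3, power 99.9%.

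| m = 3, 267 per arm | Main effect, baseline as response | Group-by-time | Baseline-adjusted |
|---|---|---|---|
| d = 0.25, rho 0.5 to 0.8 | 78% to 65% | 85% to 99.9% | 99.4% to >99.9% |
| d = 0.20, rho 0.5 to 0.8 | 59% to 47% | 65% to 97% | 95% to 99.8% |

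**Baseline imbalance.** Take b = 0.10 SD in favour of the IoT group, persisting over follow-up.
- True d = 0.25, m = 3: the main effect expects 0.10 + 0.1875 = 0.29, above the truth.
- True d = 0, rho = 0.7, m = 3: V = 0.775, SE = 0.0762, 0.10/0.0762 = 1.31, rejection about 26%.
- Unadjusted t-test at one visit, d = 0: SE = √(2/267) = 0.0865, 0.10/0.0865 = 1.16, rejection about 21%.
- Baseline as covariate, d = 0, rho = 0.7: the remaining bias is (1 − 0.7) × 0.10 = 0.03 SD; 0.03/0.0482 = 0.62, rejection about 9–10%. The bias is much smaller but not zero. Change from baseline would remove a strictly constant imbalance.

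**Incomplete records.** With an assumed 3–5% missed per visit on top of 10% attrition, 0.9 × 0.97⁴ = 80% to 0.9 × 0.95⁴ = 73% have all four follow-ups. The power cost of this is small. At rho = 0.7, d = 0.25, m = 3, going from 267 to 240 per arm moves the main effect from 69% to 64% and the baseline-adjusted analysis from 99.9% to 99.8%.

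**The case against.** The strongest reply is that the article does not commit to the bad analysis. It never says that baseline is a response or that the group main effect is the test. The role of baseline and the tested contrast are commonly left to an analysis plan, which is not shown. That stands, and it makes the dilution conditional.

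Three stronger readings are tempting, and the document supports none of them:

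- **That the treatment effect is shrunk by construction.** Group-by-time is not diluted, and from rho = 0.7 at d = 0.25 it is within about 2 points of the baseline-adjusted analysis. With preference-based allocation the main effect may be inflated instead.
- **That anyone with a missed visit is dropped.** GEE, the named alternative, uses all available visits, and item (4) plans imputation. What remains is that standard repeated-measures ANOVA needs complete records, so it leans on an imputation rule that leaves the variables unnamed and also allows single imputation.
- **That power for these outcomes is far too low.** The article states no effect, SD, correlation or power for them, so the size of any loss depends on assumed values and on the term tested.

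It can also be said that covariates could be added to GEE and that the Discussion mentions regression and propensity scores. Both are true. But the choice between GEE and ANOVA stays open, possibly until after data are seen, and the section that defines the analyses names no adjusted model for continuous repeated outcomes. Group-by-time is also an omnibus test: it gives no single treatment estimate.

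**Conclusion.** The point holds in conditional form. What rests on the text alone: section 3.4 permits repeated-measures ANOVA and unadjusted t-tests as between-group analyses of 6MWD, CAT, SGRQ and spirometry, and the models it names for adjustment do not suit them. The promise in section 2.4 cannot be kept with those models.

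What rests on algebra: if baseline is a level of time and the group main effect is read, a constant effect is diluted by 25% (6MWD) or 20% (four follow-ups, assumed) in balanced groups, and any imbalance is added in full.

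What rests on assumptions: the 65–78% against at least 99% power, and the roughly 21–26% false rejections at a 0.10 SD imbalance.

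Given how groups are formed, the bias from imbalance matters more than the loss of power. These are secondary outcomes, so this should be corrected but does not undermine the primary analysis.

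**What to change.** In section 3.4, remove repeated-measures ANOVA and unadjusted t-tests as between-group analyses of 6MWD, CAT, SGRQ and spirometry. Name one linear mixed model per outcome (or GEE with multiple imputation) with:

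- follow-up visits only as responses, using all available visits;
- group, visit and group-by-visit;
- the outcome's own baseline value as covariate;
- the same confounder or propensity adjustment as the primary analysis;
- one named contrast, such as the group difference at month 12.

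Drop single imputation for these outcomes. Report change from baseline as a sensitivity analysis: in non-randomised groups the two ways of using baseline can give different answers, and a clear difference should be reported and discussed.

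The cost is a change of wording and a few lines of R, which the protocol already names. The downsides are reliance on data being missing at random given what was observed, and some residual bias if a baseline imbalance simply persists.

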### Sample size calculation

2.3

The primary outcome measure is the 12-month rate of moderate-to-severe AECOPD. Based on prior literature, the annual exacerbation frequency in patients with moderate-to-severe COPD ranges from 0.5 to 3.0 events, of which approximately 60% are classified as moderate or severe. Assuming a two-sided significance level (*α*) of 0.05 and a statistical power (1 − *β*) of 0.80, and informed by preliminary data and published evidence suggesting that PR interventions reduce exacerbation frequency by approximately 20% (risk ratio [RR] = 0.80), sample size calculations performed using PASS 2023 software indicated a requirement of 267 participants per group. Accounting for an estimated attrition rate of 10%, which is considered feasible given the chronic disease management context in the Shijiazhuang region, a 10% inflation factor was applied, yielding a final required sample size of 294 participants per group and a total sample of 588 participants.

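### Section 3.4(3) puts pulmonary function, a set of continuous secondary outcomes, under logistic or Cox regression and among the primary outcomes, and no adjusted linear model is named for it

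*Protocol article*

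**What the plan says.** Section 3.1.2 (Secondary outcomes) lists pulmonary function as "measured using a portable spirometer, capturing FEV₁ % predicted, FVC, and peak expiratory flow (PEF"), three continuous quantities. Section 2.5.1.3 schedules spirometry at clinic visits at 1, 3, 6 and 12 months.

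Section 3.4 (Statistical analysis) treats outcomes in two places:

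- Item (2) keeps continuous outcomes on their own scale (t-test, Mann–Whitney, repeated measures ANOVA or GEE) but names no covariates.
- Item (3) is the covariate-adjusted analysis, with age, sex, comorbidities and smoking history among the confounders. It covers "primary outcome measures (e.g., pulmonary function improvement, AECOPD frequency, readmission rate), multivariable logistic regression or Cox proportional hazards models will be employed".

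Two other places promise adjustment in general terms. Section 2.4 says: "Baseline characteristics of both groups will be rigorously compared and statistically adjusted in all subsequent analyses". The Discussion adds multivariable regression and propensity score analyses, without saying which model serves which outcome.

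**The concern.** Logistic regression of improvement needs a category, so the change in FEV₁, FVC or PEF has to be cut at a threshold. Cox regression needs an event time, but spirometry is taken at fixed visits, so a time to improvement would mainly reflect the visit schedule. Neither model takes the measured value as its outcome.

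This matters more here than in a randomised trial. Groups are formed by patient preference and technology readiness, and section 3.2 accepts that they may differ in age, education, motivation and adherence. The adjusted comparison is therefore the one that can be interpreted. The second objective in the Introduction asks whether the model improves pulmonary function. Under item (3), the adjusted answer would be an odds or hazard ratio for crossing a threshold. It would not be a difference in % predicted or in litres, and it would be less precise than the same data allow.

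Item (3) also calls pulmonary function a primary outcome measure. Sections 2.3 and 3.1.1 name one primary outcome, the 12-month rate of moderate-to-severe exacerbations.

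**Working it through.** **Text side by side.** Scale of the outcome: continuous (3.1.2). Rank: secondary (3.1.2), against primary (3.4(3)). Continuous-scale methods: named without covariates (3.4(2)). Adjusted model named for spirometry: logistic or Cox (3.4(3)). General adjustment promises: no model type given (2.4 and Discussion). No linear regression, ANCOVA or covariate-adjusted mixed model is named anywhere for spirometry.

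**Inputs from the article.** Section 3.4(5): "all statistical tests will be two-sided, with a significance level of" 0.05. Section 2.3: "a statistical power (1 − *β*) of 0.80" and "indicated a requirement of 267 participants per group".

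**What 267 was sized for.** Section 2.3 states that "PR interventions reduce exacerbation frequency by approximately 20"% (RR 0.80), and of exacerbations, "of which approximately 60% are classified as moderate or severe". Reading the 60% as a control proportion gives 0.60 against 0.48, and the unpooled two-proportion formula gives

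n = (1.960 + 0.842)² × (0.60×0.40 + 0.48×0.52) / 0.12² = 266.9, so 267.

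This reproduces the stated figure. It also shows that 267 and 80% power belong to the exacerbation outcome. The article gives no effect, SD or threshold for spirometry, so everything below rests on assumed values.

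**Information kept after a cut** (normal outcome, small shift). Let p₀ be the share of controls counted as improved and c = z(1 − p₀). Relative efficiency is φ(c)² / [p₀(1 − p₀)]:

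- p₀ = 0.50: 0.3989² / 0.25 = 0.637, like analysing about 170 of 267 per group (0.637 × 267).
- p₀ = 0.30: 0.576.
- p₀ = 0.20: 0.2800² / 0.16 = 0.490, like about 131 of 267.
- p₀ = 0.10: 0.342.

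**Illustrative power.** Set the effect so that the continuous comparison has 80% power with 267 per group:

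d = (1.960 + 0.842) × √(2/267) = 0.242 SD.

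Then p₁ = 1 − Φ(c − d), and power = Φ{(p₁ − p₀) / √[p₀(1 − p₀)/267 + p₁(1 − p₁)/267] − 1.96}.

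| Controls improved | p₁ | Power after cut | Loss from 80% |
|---|---|---|---|
| 50% | 0.596 | 60.8% | 19.2 points |
| 30% | 0.389 | 58.5% | 21.5 points |
| 20% | 0.275 | 52.9% | 27.1 points |
| 10% | 0.149 | 41.0% | 39.0 points |

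A pooled-variance test gives nearly the same losses: 19.5, 21.9, 27.4 and 39.2 points.

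**Sensitivity to the assumed effect** (cuts with 20% to 50% of controls improved, 267 per group):

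- 0.15 SD: continuous power 41%, loss about 13 to 17 points.
- 0.30 SD: continuous power 93%, loss about 15 to 22 points.
- 0.40 SD: continuous power above 99%, loss 7 points or less. With only 10% of controls improved, it is still about 16 points.

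These are unadjusted two-group calculations. They show the cost of the cut, not the power of any adjusted model in this study.

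**The case against.** The strongest reply is that the article, read as a whole, already allows an adjusted continuous analysis. Spirometry is repeated, so it falls under the GEE option in item (2). GEE accepts covariates, section 2.4 promises adjustment throughout, section 3.2 lists baseline pulmonary function as a covariate, and the Discussion mentions multivariable regression without limiting it to logistic or Cox. The improvement variable in item (3) may also be a derived responder measure that supplements the continuous ones.

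Much of this stands. A reader might infer that the plan forces FEV₁, FVC and PEF to be dichotomised and rules out any other adjusted analysis. The documents do not support that: an adjusted continuous analysis remains open. But none of these places names a linear adjusted model for spirometry, while item (3) does name a model family for it, and that family does not fit the scale. This is a stated choice that fits badly, not a detail left for later.

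A reader might also take 20 to 27 points as the power this trial will lose. It is not a property of the trial, because the effect, the threshold and the 80% power for spirometry are all assumed.

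Finally, a reader might infer that an unstated threshold inflates the type I error. No passage proposes trying several cuts, and the threshold itself may be set in a SAP that is not shown, so no error rate can be attached to the plan on that ground.

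**Conclusion.** The mismatch is real and should be corrected. Item (3) assigns continuous secondary outcomes to models for binary or time-to-event data and labels them primary, in a study where the adjusted analysis carries the comparison.

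The retained information (about 64% at a median cut, about 49% when 20% of controls improve) assumes normality and a small shift. The power cost is an illustration: about 19 to 27 points in the central case, about 39 with 10% of controls improving, and 7 or less at 0.40 SD or more with 20% to 50% improving.

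The consequence is confined to a secondary endpoint. The sample size and the primary outcome do not depend on it.

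**What to change.** In section 3.4(3), remove pulmonary function from the logistic/Cox sentence and from the list of primary outcome measures. State that FEV₁ % predicted, FVC and PEF will be analysed as continuous values in a linear mixed model or identity-link GEE. The terms would be group, visit, group-by-visit, the baseline value of the same measure and the study's confounder set. Report the adjusted mean difference at 12 months with its 95% confidence interval. Keep any responder analysis supportive, with its threshold fixed in advance.

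The cost is a few sentences of analysis text. Baseline spirometry and the covariates are already to be collected (section 3.2), so no further patients, visits or data are needed. The small downside is that there is no headline odds ratio for improvement, though it can still appear as a supportive result.
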